## Endpoints

### Primary endpoint

#### *Progression Free Survival*

Progression free survival is defined as the length of time from inclusion to the first documentation of one of the following:

**PSA progression** defined according to American Society for Therapeutic Radiology and Oncology (ASTRO) Phoenix definition: nadir PSA + 2 ng/mL (on three consecutive measurements with at least one month between each)

or

**Death** due to any cause

or

**Radiological disease progression**, locally or as metastatic disease.

Due to potential “PSA bounce” during the first 24 months after treatment, a PSA rise >2 ng/mL may not be deemed as progression by the treating physician until after the clinical window of a bounce is excluded. The date for progression will then be corrected.

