#### **Trial period**

Patient recruitment is calculated to take 18 months and follow-up time 60 months

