#### *Quality of Life*

### Follow up

During the first year after treatment the patients will be seen by treating oncologist for clinical evaluation every 6 months ( $\pm$  14 days). Additional visits at treating physician’s discretion.

During the follow up between 12-60 months the patient may be referred to their home clinic and followed by urologist every 6 months ( $\pm$  28 days) or until progression. The 36 months-visit however, will take place at NUS, where a biopsy to investigate local control will be performed.

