| PET-MRI (imaging
intense)                                      | X                  | X           | X         |              | X                                 |                                             |                                    |                                    |                                    | X                                  |                                       |
| MRI
(imaging non
intense)                                   | X                  | X           |           |              |                                   |                                             |                                    |                                    |                                    |                                    |                                       |
| Blood tests: PSA,
Hb, Creatinine,
Testosterone, ALP         | X                  | X           |           |              | X                                 | X                                           | X                                  | X                                  | X                                  | X                                  |                                       |
| UCAN-samples                                                      | X                  | X           |           | X            | X                                 |                                             | X                                  |                                    |                                    | X                                  |                                       |
| Quality of Life                                                   | X                  |             |           | X            | X                                 | X                                           |                                    | X                                  |                                    | X                                  | 5 years*                              |
| Physician, safety                                                 | X                  | X           |           | X            | X                                 | X                                           | X                                  | X                                  | X                                  | X                                  |                                       |

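### The protocol does not fix the date of a PSA event, the bounce criterion or PSA testing after month 36, and does not require the historical controls to be read by the same rule

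*Protocol*

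**What the plan says.** **Event rule.** Protocol, Progression Free Survival: "Progression free survival is defined as the length of time from inclusion to the first documentation of one of the following". The PSA component is "nadir PSA + 2 ng/mL (on three consecutive measurements with at least one month between each". Death from any cause and radiological progression are the other components.

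**Bounce clause.** In the same section, for the first 24 months after treatment, a rise "may not be deemed as progression by the treating physician until after the clinical window of a bounce is excluded". The next sentence reads "The date for progression will then be corrected". The section gives neither the criterion for a bounce nor the date to which the correction goes.

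**Schedule.** In the Flowchart, the row "Blood tests: PSA, Hb, Creatinine, Testosterone, ALP" is marked before radiotherapy, at its start, and at 6, 12, 18, 24, 30 and 36 months after its end. The last column, for six-monthly assessments up to the endpoint, is empty in this row; the quality-of-life row has an entry there. Trial period states "Patient recruitment is calculated to take 18 months and follow-up time 60 months". Follow up says that between 12 and 60 months "the patient may be referred to their home clinic and followed by urologist every 6 months", without naming PSA.

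**Comparison.** Study design compares PFS with 100 historical controls matched on T stage, PSA and Gleason score. Neither that section nor Statistical methods says how progression is read in the controls.

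**The concern.** An event that needs three values can be dated at the first or at the third. The definition runs to first documentation, which most naturally means the third value, but the protocol does not say so. If a withheld bounce is corrected back to the first rise, the trial group would contain two dating conventions.

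The bounce decision rests with a physician who knows the treatment, since the trial has one open arm. On the flowchart's own schedule, a first rise at month 30 or 36 has no marked draws to confirm it.

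The only comparison is with non-randomised controls. Its minimum condition is that an event is found and dated in the same way in both groups. If the groups differ in this, PFS can differ with no treatment effect.

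**Working it through.** **The plan's own figure.** Power considerations gives 86 patients for a 20% improvement in 3-year freedom from relapse, with 80% power and two-sided 0.05. The control rate is missing, so 86 cannot be reproduced uniquely. The formula used is n = [1.96·√(2p̄q̄) + 0.842·√(p₁q₁ + p₂q₂)]² / (p₂ − p₁)². Read as 20 points absolute, 60% vs 80% needs 82 per group and 55% vs 75% needs 89; 86 per group fits control rates of 56-58% (or 22-24%). The benchmark of 20 points is therefore itself a reading.

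**Timing.**
1. Inclusion to end of radiotherapy: 3 months of prior hormonal treatment plus 35 fractions at 5 per week (7 weeks, 1.6 months) = 4.6 months.
2. Three years from inclusion is therefore 36 − 4.6 = 31.4 months after radiotherapy.
3. On 6-monthly draws the third value comes 12 months after the first. A first rise at month 18 is confirmed at month 30, before the landmark. First rises at months 24 and 30 are not confirmed by then, and count as event-free if the event is dated at confirmation.
4. On the flowchart, a first rise at month 24 is confirmed at month 36. First rises at months 30 and 36 need draws at months 42 and 48, which are not marked.

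**Size if only the trial group is dated late.** Assumptions, none from the documents: exponential event times, no true effect, controls dated at the first value, trial PSA events dated d months later, and a share w of the hazard from PSA events. With true 3-year rate S, the observed trial rate is S^[w(36 − d)/36 + (1 − w)].

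Example, S = 0.60, w = 1, d = 12: 0.60^(24/36) = 0.711, a gain of 11.1 points. With w = 0.7 the exponent is 0.7 × 24/36 + 0.3 = 0.767 and the rate is 0.676, a gain of 7.6 points.

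The table shows the observed rate in %, with the gain in points and the chance of a significant result favouring the trial in parentheses. That chance comes from a pooled two-proportion z test, 86 vs 100, ignoring the matching; its nominal value is 2.5%.

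| True rate | d = 2, w = 1 | d = 6, w = 1 | d = 12, w = 1 | d = 12, w = 0.7 |
|---|---|---|---|---|
| 50% | 52.0 (+2.0; 4.5%) | 56.1 (+6.1; 13.0%) | 63.0 (+13.0; 42.8%) | 58.8 (+8.8; 22.2%) |
| 60% | 61.7 (+1.7; 4.3%) | 65.3 (+5.3; 11.2%) | 71.1 (+11.1; 35.4%) | 67.6 (+7.6; 18.6%) |
| 70% | 71.4 (+1.4; 4.0%) | 74.3 (+4.3; 9.4%) | 78.8 (+8.8; 27.5%) | 76.1 (+6.1; 14.9%) |

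**Check on the visit grid, S = 0.60.** The month-18 and month-30 draws fall 22.6 and 34.6 months from inclusion. Dating at the third 6-monthly value counts first rises up to 22.6 months: 0.60^(22.6/36) = 72.6%. Dating at the first value counts them up to 34.6 months: 0.60^(34.6/36) = 61.2%. The gap is 11.4 points, close to the continuous model. A 2-month confirmation on this grid loses the month-30 draw (34.6 + 2 = 36.6, past the landmark). The last counted draw is then at 28.6 months: 0.60^(28.6/36) = 66.6%, a gap of 5.4 points. The 1-2 points for d = 2 thus belong to the continuous model.

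**Same rule in both groups.** With equal d and equal PSA frequency, both rates shift alike and the bias is about zero, apart from rises never confirmed.

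**The case against.** The strongest reply is that the documents say nothing about control ascertainment. A reader might infer that historical controls cannot be held to a three-value rule, so that the bias must favour the trial. The protocol does not support that: the rule could be run on the controls' PSA series, and if these are sparser the bias could run the other way. This part of the reply stands.

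A reader might also take the bounce clause as a licence to remove events. It is a temporary withholding followed by a date correction. What remains is that the criterion and the corrected date are undefined.

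Nor does the empty flowchart cell show that PSA testing stops at month 36. The physician row is empty in the same column, although the Follow up section plainly continues those visits. Chart and text disagree, which calls for reconciliation. The gap reaches the 3-year figure only through confirmation of a month-30 rise; otherwise it affects later PFS.

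The 12-month delay is an upper case. One month between values is a minimum, so earlier repeats are allowed, and extra visits are permitted at least in the first year. Death and radiological progression are not delayed by the PSA rule.

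Finally, event dating and the reading of controls are often left to a statistical analysis plan, and silence alone would be no fault. But the protocol itself sets the three-value rule, the physician's discretion and the draw schedule. A later plan cannot recover PSA values never drawn, or reconstruct bounce decisions made without a criterion.

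**Conclusion.** The point holds as a defect in how the primary endpoint is fixed. Following the stated rule and chart can delay PSA events or leave them unconfirmed, and makes event calling subjective in the first 24 months. No common ascertainment is required for the two groups being compared.

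If only the trial group is dated at the third value, the 3-year rate is inflated by about 1-2 points (2-month delay, continuous model) up to 9-13 points (three 6-monthly values, all events PSA events), for true rates of 50-70%. The upper case is 6-9 points if PSA events are 70% of the hazard. The 11-point gain and 35% chance of a false positive at a true rate of 60% are an upper-case illustration, not an expected bias. The size rests on assumptions that the documents neither confirm nor exclude, and the direction is not settled.

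**What to change.** 1. **One PSA rule for both groups**, applied by program to the raw PSA series of trial patients and controls. The event is dated at the first value at or above nadir + 2, once confirmed; confirmation decides whether it counts, not when.
2. **An objective bounce criterion** in place of physician discretion, for endpoint classification only: a rise is cleared if a later value, taken without new treatment, is back below nadir + 2. If any date correction is kept, state its target date.
3. **Unconfirmed rises**: state how the endpoint counts a rise never confirmed because further treatment began.
4. **Schedule**: reconcile the Flowchart with Trial period and Follow up by entering PSA in the last column to 60 months.
5. **Testing frequency**: report PSA intervals in both groups, because a common rule does not by itself remove the effect of sparser testing.

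The cost is a small amendment, some programming, retrieval of the controls' PSA series, and a few provisional events later cleared by rule.

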## **Dose escalation with SIB to intraprostatic/lymphatic GTV in high risk prostate cancer**

### ***Method***

#### **Study design**

The present study will be performed as a single institute prospective consecutive phase II clinical trial with matched historical controls of dose escalation to intra prostatic tumor and, if eligible, to radiological lymph node metastasis in the pelvis.

Patients are recruited consecutively during their consultation at Cancer Centre, Umeå University Hospital, after given both oral and written patient information and due time for consideration.

All patients included in the present study will receive external radiotherapy (RT) of 2,2 Gy to 77 Gy to the prostate in 35 fractions and pelvic nodal radiotherapy of 1,6 Gy to 56 Gy in 35 fractions. A simultaneous integrated boost (SIB) of 84 Gy in 35 fractions (fractional dose 2,4 Gy) will in addition be delivered to macroscopic tumor in the prostate. In case of radiological suspected metastasis in one or more of the pelvic lymphatic nodes according to PET/CT-scan an additional SIB of 70 Gy in 35 fractions (fractional dose 2 Gy) will be delivered to PET-positive nodules.

At baseline QoL questionnaire and baseline symptoms will be collected after given informed consent. Renewed QoL and symptom scoring will be collected at end of treatment and during follow up. A historical control group of 100 consecutive patients receiving external radiotherapy to prostate/pelvic lymph nodes without dose escalation to the intra prostatic macroscopic tumor will be used to compare PFS, OS, LC and QoL. Matching criteria is T-stadium, pre-treatment PSA and GS.

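### Primary endpoint: the PSA-bounce clause has no PSA criterion, no stated target for the corrected date, and no matching rule for the historical controls

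*Protocol*

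**What the plan says.** All of the rule stands in the protocol under Endpoints, Progression Free Survival. The clock is set first: "Progression free survival is defined as the length of time from inclusion to the first documentation of one of the following". The listed events are PSA progression, death from any cause, and radiological progression "locally or as metastatic disease". PSA progression is the Phoenix threshold of nadir plus 2 ng/mL, required "on three consecutive measurements with at least one month between each".

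A closing paragraph then qualifies the PSA event. It cites a possible bounce within 24 months of treatment, and says that a rise of more than 2 ng/mL seen in that period "may not be deemed as progression by the treating physician until after the clinical window of a bounce is excluded". The paragraph ends with this sentence: "The date for progression will then be corrected".

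The comparator is described under Study design: "A historical control group of 100 consecutive patients receiving external radiotherapy to prostate/pelvic lymph nodes without dose escalation". The escalation meant there is the boost to macroscopic tumour within the prostate. That section gives the matching factors and the outcomes to be compared. It does not say how progression is ascertained in the controls.

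**The concern.** The first part of the definition can be applied by anyone holding the PSA series. The closing paragraph cannot, for four reasons:

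- It does not say what PSA pattern makes a rise a bounce, or what excludes one.
- It does not say to which date progression is corrected: the first rise, the third value, the end of the window, or a later visit.
- It does not say whether it concerns only a rise not yet confirmed, or also one already held on three values. The three-value requirement itself filters out short-lived rises, so the paragraph either adds little or can override the rule.
- It does not say that the historical controls are classified in the same way.

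The trial is one prospective cohort set against past patients, and no masked assessment is described. Under Follow up, patients may be followed by a urologist at their home clinic from month 12, so the treating physician may be several people without a shared criterion. The clause can postpone or remove a PSA event but cannot create one. If it works only in the trial cohort, any error it causes runs in one direction.

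**Working it through.** **The plan's own figure.** Power considerations gives 86 patients for a 20% improvement at three years (80% power, two-sided 0.05), without a control rate. With p̄ the mean of the two rates,

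n per group = [1.96·√(2p̄(1−p̄)) + 0.842·√(p₁(1−p₁)+p₂(1−p₂))]² / (p₂−p₁)².

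Reading 20% as absolute, 57% v 77% gives (1.303 + 0.547)²/0.04 ≈ 85.6, so 86 per group. The figure is attainable, but only by choosing a control rate. Nothing below depends on it except the cohort size.

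**Timing.** Inclusion is 3 months before radiotherapy (Flowchart). Radiotherapy is 35 fractions at 5 per week, which is 7 weeks or about 1.6 months (Dose specifications). Taking the window as 24 months from the end of radiotherapy, it closes at 3 + 1.6 + 24 ≈ 28.6 months from inclusion. That is before the three-year point, if three years also runs from inclusion. What follows depends on the date rule:

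| Date given to a deferred progression | Months from inclusion | Counted by 36 months? |
|---|---|---|
| First rise (inside the window) | up to 28.6 | yes, time unchanged |
| Close of the window | 28.6 | yes, but later |
| Third of three new values at months 30, 36, 42 after radiotherapy | 3 + 1.6 + 42 ≈ 46.6 | no |

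The last row assumes that PSA is measured at the six-monthly visits after month 36. The text supports none of the three rows over the others.

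**Illustration of lost events.** Suppose there is no true effect, both groups have three-year freedom from relapse p, and k of the 86 trial patients with progression are never reclassified while the 100 controls are unaffected. Each such patient moves the trial rate by 1/86 = 1.16 points. Then q = p + k/86, d = q − p, and p̄ = (100p + 86q)/186.

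- s₀ = √[p̄(1−p̄)(1/100 + 1/86)]
- s₁ = √[p(1−p)/100 + q(1−q)/86]
- Rejection rate = 1 − Φ((1.96s₀ − d)/s₁) + Φ((−1.96s₀ − d)/s₁)

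Example, p = 0.60 and k = 5: q = 0.658, d = 0.058, p̄ = 0.627, s₀ = 0.0711, s₁ = 0.0708. The terms are 1 − Φ(1.147) = 0.126 and Φ(−2.79) = 0.003, total 0.128.

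| k never reclassified | Shift (points) | p = 0.50 | p = 0.60 | p = 0.70 |
|---|---|---|---|---|
| 0 | 0 | 5.0% | 5.0% | 5.0% |
| 3 | 3.5 | 7.6% | 7.7% | 8.1% |
| 5 | 5.8 | 12.4% | 12.8% | 14.2% |

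Nearly all of the excess favours the boost: that tail alone goes from 2.5% to 6.9–7.5% at k = 3 and to 12.1–14.0% at k = 5. Neither k nor p is given in the protocol; both are assumed here.

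**The case against.** A reader might infer that the protocol lets the physician strike out a confirmed PSA progression for good, and so tilts the comparison towards the boost. The text does not go that far.

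- The clause defers the label and is followed by the sentence on correcting the date. Read naturally, a rise that proves to be progression is counted. With back-dating to the first rise, k is 0 and the error stays at 5%.
- The window closes before the three-year point, so a deferred event can still count there.
- The clause speaks of a rise above 2 ng/mL, not of one already held on three values. Overriding a confirmed rise is a possible reading, not a stated one.
- How bounces were handled in the controls is not described. Similar discretion there would shrink or remove the one-sidedness.
- Few confirmed runs would complete early. The Flowchart shows antiandrogen until the 12-month visit, and on six-monthly values a run starting at month 12 is complete only at month 24.

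All of this stands against a claim of demonstrated bias. It does not supply what is missing. The reassurance from the date sentence depends on a target date that the protocol does not give, and the last row of the timing table shows that another reading can carry an event past three years. Even an event moved only to the close of the window changes the progression-free time being compared.

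**Conclusion.** The point holds as a defect in the definition of the primary endpoint, not as a demonstrated inflation of error. The PSA component is fixed by an objective rule and then made subject to a judgement with no criterion, no target date, no stated order of precedence over the three-value rule, and no link to the controls. Followed as written, it can delay or remove PSA events in the trial cohort. Death and radiological progression lie outside it.

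The size runs from nothing, if every deferred progression is confirmed and back-dated, to a two-sided error of about 8–14% if 3 to 5 of 86 are never reclassified. The upper figures assume unaffected controls, no true effect, three-year freedom from relapse of 50–70%, and 86 v 100 patients. The wording should be settled before outcomes are read, because a rule chosen afterwards would carry little weight.

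**What to change.** This concerns classification of the endpoint for the analysis only, not the management of patients. Replace the closing paragraph with a rule computed from PSA values:

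- A rise to nadir + 2 ng/mL that falls back below that level before the third consecutive value, without new prostate-cancer treatment, is a bounce and not an event.
- A rise held on three consecutive values at least one month apart is an event, dated to the first qualifying value.
- The same algorithm is applied to the controls' PSA series as far as their records allow.
- The physician's opinion is kept as a recorded comment and does not alter the classification.

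The wording should also say how a patient is counted who starts new treatment before a third value is available.

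Cost: a change of protocol wording. PSA is already collected in the trial cohort (Flowchart, blood tests). The controls' PSA series must be extracted, and their intervals may differ, which should be reported alongside the comparison. An occasional bounce lasting three values will count as an event.

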#### *Local Control*

Local control is defined as negative biopsy 36 months after end of radiotherapy.

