### Secondary endpoint

#### *Overall Survival*

Overall survival is defined as the length of time from randomization to death from any cause.

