### ***Statistical procedures***

### **Power considerations**

In this extremely high risk population there is a considerable risk of relapse. Calculating on an improvement of 20% with dose-escalation and irradiation of lymph-nodes with boost to radiologically pathologic nodes we would need 86 patients to detect an increased freedom from relapse at three years with 80 % power and a two-sided significance level of 0,05.

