| Instructions on
bowel, bladder
filling. Oral and
written |                    | X           |           |              |                                   |                                             |                                    |                                    |                                    |                                    |                                       |
| Prostate Biopsy,
optional                                      |                    | X           |           |              |                                   |                                             |                                    |                                    |                                    | X                                  |                                       |

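### Local control is listed as a primary endpoint, but it is unpowered, rests on a biopsy described both as planned and as optional, and has no described control data

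*Protocol*

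**What the plan says.** **Rank.** In the Protocol's Endpoints section, the heading "Primary endpoint" is singular but has two sub-headings of equal level, Progression Free Survival and Local Control. The heading "Secondary endpoint" comes after both and opens with overall survival.

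**Error rate and power.** Power considerations sizes the trial at 86 patients to "detect an increased freedom from relapse at three years with 80 % power and a two-sided significance level of 0,05". Local control is not mentioned there. The Publication section refers to one primary endpoint, whose analysis waits for a set number of events.

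**Definition.** The whole definition is: "Local control is defined as negative biopsy 36 months after end of radiotherapy".

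**Biopsy.** Follow up says that at the 36-month visit "a biopsy to investigate local control will be performed". The Flowchart row reads "Prostate Biopsy, optional", with a mark at 36 months.

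**Comparison.** Study design says that 100 historical controls "will be used to compare PFS, OS, LC and QoL".

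**The concern.** A primary endpoint should have a clear rank, a stated error rate, a measurement that every patient is meant to have, and a result for every patient. Local control lacks all four as written.

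- If it is primary, the sample size does not cover it and the single 0.05 level is not shared with it.
- If it is not primary, the Endpoints section is wrong.
- In either case, the definition gives a result only for men alive and biopsied at month 36. A rate in that group is conditional on survival and willingness, and can look better than the rate in all 86.
- The comparison with historical controls needs the same measurement in both groups, and the Protocol does not say that it exists for the controls.

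Moving local control to secondary would not repeat what PFS already measures. PFS counts PSA progression, death and radiological progression, but not a positive biopsy, so the two endpoints can give different answers.

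**Working it through.** **1. The plan's own figure.** Inputs from Power considerations: 86 patients, an improvement of 20%, 80% power, two-sided 0.05. No control rate is given, and the 20% is not called absolute or relative, so the 86 can be neither confirmed nor refuted. It is reachable for a 20-point difference. With assumed rates of 0.55 v 0.75 and unpooled variance:

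n per group = (1.960 + 0.842)² × (0.55×0.45 + 0.75×0.25) / 0.20² = 7.849 × 0.435 / 0.04 = 85.4, so 86.

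For 86 v 100 at assumed rates of 0.50 v 0.70, power is 0.797. All of this concerns freedom from relapse; none of it covers local control.

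**2. Multiplicity, only if either endpoint counts as success.** The Protocol states no such rule. Two independent tests at 0.05 give 1 − 0.95² = 0.0975. With bivariate normal test statistics, the error is 0.091 at an assumed correlation of 0.5 and 0.070 at 0.9.

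Splitting to 0.025 each would hold it at 1 − 0.975² = 0.0494. The price is power:
- An 80% design falls to Φ(1.960 + 0.842 − 2.241) = 0.71, or needs (3.083/2.802)² = 1.21 times the patients (86 becomes about 104).
- For 86 v 100 at 0.50 v 0.70, power falls from 0.797 to 0.706.

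**3. Men without a biopsy.** The uptake is assumed; the Protocol gives none. Suppose 60 of 86 are biopsied and 54 are negative.
- Reported rate: 54/60 = 0.90.
- All 26 others counted as failures: 54/86 = 0.63.
- All 26 others counted as controlled: (54 + 26)/86 = 0.93.

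If 43 are biopsied and 39 are negative, the reported rate is 0.91 and the bounds are 39/86 = 0.45 and (39 + 43)/86 = 0.95.

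**4. How many men may have had a PFS event by then.** At an assumed 70% to 80% three-year freedom in the trial group, 86 × 0.20 = 17 to 86 × 0.30 = 26 men. The biopsy falls later than three years from inclusion: about 3 months before radiotherapy, 7 weeks of treatment (35 fractions at 5 per week, about 1.6 months) and 36 months after, or roughly 40.6 months. The count is therefore low if anything. It counts men with an event, not men known to miss the biopsy.

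**5. Power for a local control comparison.** Assume local control of 0.60 in controls v 0.80 in the trial group, with all 100 controls biopsied. Power is 0.848 with 86 trial biopsies, 0.759 with 60 and 0.653 with 43. If the controls have no 36-month biopsy, the comparison cannot be made under the stated definition.

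**The case against.** **Local control may be primary only through a layout slip.** The singular heading, the power statement and the Publication section all point to PFS. This is a fair reading, but the document does not say so, and correcting it costs one line.

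**A multiplicity rule may be in an SAP.** This stands. A missing alpha split is not itself the fault. A reader might infer that the trial's error rate is 9.75%, but that needs an either-endpoint rule that the Protocol never states. If both endpoints had to succeed, no split would be needed. If the local control comparison cannot be made, there is no second comparative test to inflate the error. What remains is that the Protocol itself leaves the endpoint's rank unsettled.

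**Progressors may still be biopsied.** A reader might infer that men who progress never reach the month-36 biopsy, because Follow up lets the six-monthly visits end at progression. The documents do not settle this: Follow up treats the 36-month visit separately, and Withdrawal from treatment keeps patients in follow-up until the endpoints are reached, whatever treatment they later receive. Deaths and refusals leave the gap on any reading.

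**Historical patients cannot be scheduled for a biopsy.** True, and their records may contain one. The supportable point is only that no source is described.

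**Local failure from charts could replace the biopsy in both groups.** This is tempting, but the Protocol does not say what control records contain. In the Flowchart, scheduled imaging after radiotherapy (PET-MRI at 6 and 36 months) is only for the more intensively imaged patients, so radiological local failure would be found unevenly even within the trial group.

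**Conclusion.** The point holds. Local control is placed as primary but is not powered, and the Publication section's single event-driven primary endpoint does not fit it. Its only measurement is described in two incompatible ways, the definition leaves some men without a result, and no source of control data is given.

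The firm part needs no assumptions, because it rests on the text alone. The sizes are illustrative:
- bounds of 63% to 93% around a reported 90%, under assumed biopsy uptake;
- 17 to 26 of 86 men with a PFS event by three years, at an assumed 70% to 80% freedom;
- family-wise error up to 9.75%, or about 7% to 9% at assumed correlations of 0.9 to 0.5, and only under an either-endpoint rule.

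A reader might stretch the count of men with an event to 34 of 86 by using 60% freedom (86 × 0.40). In a 60% v 80% scenario, however, 60% is the control rate and does not apply to the trial patients.

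**What to change.** 1. Name PFS the sole primary endpoint and list local control as secondary. Alpha and the 86 do not change.
2. Reconcile Follow up with the Flowchart on whether the 36-month biopsy is planned for all or optional, and Follow up with Withdrawal from treatment on whether men who have progressed still attend for it.
3. Extend the definition: count documented local progression before month 36 as local failure, report how many men were not biopsied and why, and give worst-case and best-case bounds over all 86. State that imaging before month 36 differs between patients.
4. Report biopsy-defined local control descriptively in the trial group only. If comparable 36-month biopsies exist for the controls, say so, give their source and keep the comparison.

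If the sponsor wants local control to stay primary, the Protocol must state the success rule, and the sample size must be re-derived for local control.

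The cost is amendment wording and collecting reasons for missing biopsies. Local control loses its primary status and, without control biopsies, its formal comparison.
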